## Abstract

**Aims:**

Precision nutrition, guided by genetic testing, has emerged as a promising approach for managing obesity. However, robust clinical trials testing its effectiveness in real‐world dietary interventions remain scarce. The GenOn Programme aims to evaluate whether tailoring nutritional care based on genetic risk for obesity enhances weight loss, satiety control, and metabolic outcomes in adults with overweight and obesity.

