Unlike conventional nutritional practices, precision nutrition promotes better health outcomes by considering individual genetic variations that directly impact nutrient metabolism.^13^ In this sense, its strategy focuses on detecting individual biomarkers, allowing the application of more personalised and effective nutritional interventions to improve both prevention and treatment of obesity.^7^

The GenON Programme is a personalised nutritional intervention study conducted at the Universidade Federal de Viçosa in partnership with the Brazilian Ministry of Health, which has as its primary outcome to investigate the effect of a personalised diet that targets satiety control on body weight changes in carriers of single nucleotide polymorphisms (SNPs) in the FTO, MC4R and LEP genes. In this sense, since we believe that nutritional treatment of obesity may be more effective when the individual's genetic profile is considered, this randomised controlled trial aims to develop a genetically based personalised intervention for the nutritional care of people with overweight or obesity, representing an innovative approach to optimising the treatment of these individuals.

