### Study design

2.1

The GenOn Programme is an 18‐week, 2 × 2 factorial, randomised controlled trial enrolling 120 adults of both sexes who present with overweight or obesity. The study of factors involves comparing genetic risk for obesity with nutritional interventions.

During screening visits, selected participants will be evaluated a priori for their genetic score and classified as low risk (LR) or high risk (HR) for obesity. Before intervention, participants will be randomly allocated into control or satiety intervention according to their risk classification, composing four experimental groups (control low‐risk group; control high‐risk group; intervention low‐risk group; intervention high‐risk group).

At the beginning and after 12 and 18 weeks, participants will attend the laboratory after a 10 to 12‐h fast and without water consumption, carrying 24‐h food records (three non‐consecutive days, including one weekend day) and faecal samples, to perform the study assessments. Participants will be evaluated for anthropometric and body composition analysis, questionnaire completion, blood sample collection and dietary prescription, in accordance with their assigned intervention group. Dietary interventions consist of 5 cal‐restricted nutritionally balanced plans (control intervention) or similar plans adapted to improve satiety, plus inclusion of granola (satiety intervention). All participants will receive biweekly individualised dietary counselling to promote healthier food behaviour, with emphasis on reducing the consumption of ultraprocessed foods, as recommended by Brazilian^14^, ^15^ and international^16^ guidelines. For the satiety group, granolas will be delivered, and compliance will be checked during individual counselling. Biweekly group psychological counselling, based on the experience of encounter groups, will be used to support self‐care, increase the sense of belonging to the programme and reduce dropout during the 18‐week follow‐up period. Furthermore, group counselling will be provided to address the psychological and behavioural aspects that influence the treatment of overweight and obesity, particularly among all treatment groups (Figure 1).

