### Statistical analysis

2.28

Statistical analyses will be performed using SPSS software, version 24.0 (SPSS Inc., Chicago, IL, USA). Quantitative variables will be expressed as mean ± standard deviation (SD) or median (with 25th–75th percentiles), whereas qualitative variables will be presented as frequencies (percentages). Data normality will be assessed using the Kolmogorov–Smirnov test, and logarithmic transformation will be applied when distributions deviate from normality. Baseline differences between groups will be examined using the chi‐square test for qualitative variables and the independent‐samples Student's *t*‐test for quantitative variables.

A mixed ANOVA will be applied to determine the effects of groups (control low‐risk group; control high‐risk group, intervention low‐risk group, intervention high‐risk group), time (baseline, 12 weeks and 18 weeks) and genotype (LR and HR). Effect sizes will be calculated as partial eta‐squared (*ηp*
^2^), classified as small (0.01–0.05), moderate (0.06–0.13) or large (≥0.14).^56^ Bonferroni‐adjusted estimated marginal means will be used for post hoc comparisons. Variables violating homogeneity assumptions serão log10‐transformed. One‐way ANOVA will be used to compare changes in the evaluated variables between the control and intervention groups.

Linear and nonlinear regression models will be explored to estimate the association between variables with significant correlation. The statistical significance criterion will be *p* ≤ 0.05.

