## CONCLUSION

4

The GenOn Programme is a nutrition precision approach guided by genetic testing, which can achieve better efficacy in the treatment of overweight and obesity, demonstrating to the nutritionist and the multidisciplinary team the clinical value of genetically guided nutritional care in improving outcomes for this population.

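### The mixed ANOVA lists genotype alongside a four-level group factor that already contains it, and no planned term or contrast isolates the diet × genotype effect that the genetic claim needs

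*Protocol article*

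**What the plan says.** Section 2.1 (Study design) calls the trial a 2 × 2 factorial and explains: "The study of factors involves comparing genetic risk for obesity with nutritional interventions". On allocation it says that "participants will be randomly allocated into control or satiety intervention according to their risk classification", which produces four cells. Both diets are given in both risk classes.

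Section 2.28 (Statistical analysis) then states: "A mixed ANOVA will be applied to determine the effects of groups". The levels listed for that factor are the four diet-by-risk cells. The same sentence continues with "time (baseline, 12 weeks and 18 weeks) and genotype (LR and HR". Two other comparisons follow: Bonferroni-adjusted post hoc comparisons of estimated marginal means, and a one-way ANOVA of changes between the control and intervention groups.

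The abstract (Aims) asks "whether tailoring nutritional care based on genetic risk for obesity enhances weight loss". Section 4 (Conclusion) speaks of "the clinical value of genetically guided nutritional care in improving outcomes for this population". The Introduction words the primary aim differently, as to "investigate the effect of a personalised diet that targets satiety control on body weight changes in carriers of single nucleotide polymorphisms".

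**The concern.** There are two linked faults in section 2.28.

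- **The factors are listed wrongly.** Each level of the group factor names a risk class, so genotype is an exact function of group and cannot have an effect of its own once group is in the model. Two-level diet, which is the randomised factor, does not appear in the mixed ANOVA at all, although section 2.1 describes a diet-by-risk factorial.
- **The key contrast is absent.** No arm assigns diet according to genotype. A benefit of the satiety diet over control, averaged over risk classes, would support that diet for everyone, genotyped or not. Only a difference in the diet effect between high and low risk bears on whether genetic information adds anything.

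At stake is the headline conclusion. The trial could report group differences, or a significant diet effect in the high-risk cells only, and present either as evidence for genetic guidance without having tested effect modification.

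**Working it through.** The plan gives no figure for the diet × genotype effect, so there is none to reproduce. The 30 per group and 30% loss in section 2.7 serve only as inputs.

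**1. Aliasing.** Take 120 participants, 30 in each of four cells.

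| Between-subject terms | Columns | Rank |
|---|---|---|
| Intercept + group (3 indicators) | 4 | 4 |
| The same + genotype | 5 | 4 |
| The same + group × genotype | 8 | 4 |
| Diet, genotype, diet × genotype (with intercept) | 4 | 4 |

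The residual of genotype after regression on group is zero to machine precision. Genotype therefore has 0 df once group is in. If genotype is entered first, group keeps 2 df, which pool the diet main effect with diet × genotype. In neither order is the 1-df interaction separated.

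**2. What each planned comparison estimates.** Write the mean changes as SH, SL (satiety, high and low risk) and CH, CL (control, high and low risk).

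- Interaction needed: (SH − CH) − (SL − CL).
- One-way ANOVA of changes, equal cells: (SH + SL)/2 − (CH + CL)/2. Multiplying its weights by those of the interaction and summing over SH, CH, SL, CL gives 0.5 + 0.5 − 0.5 − 0.5 = 0. The two are orthogonal, so this comparison carries no information on the interaction.
- Post hoc pairs: four cells give 6 pairs. Two are pure diet effects within a risk class (SH v CH, SL v CL), two are pure genotype differences within a diet, and two change both. None is a difference of differences. A significant SH v CH with a non-significant SL v CL does not test whether the two differ.

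**3. Cost of the factorial form.** It spans the same four-dimensional space. The 3 between-group df split into diet 1, genotype 1 and diet × genotype 1. The diet × genotype × time test has 2 df, and a single change score gives a 1-df contrast.

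**4. Precision of that contrast.** The document gives no interaction size, so 1.0 and 0.5 SD of the change score are assumptions. With n per cell, the standard error is √(4/n) SD. After 30% loss, n = 30 × 0.7 = 21.

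- n = 30: SE = √(4/30) = 0.365 SD.
- n = 21: SE = √(4/21) = 0.436 SD.

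Power at two-sided 5% is approximately Φ(Δ/SE − 1.96):

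| Δ | n = 30 per cell | n = 21 per cell |
|---|---|---|
| 1.0 SD | Φ(2.74 − 1.96) = 78% | Φ(2.29 − 1.96) = 63% (62% by non-central F) |
| 0.5 SD | Φ(1.37 − 1.96) = 28% | Φ(1.15 − 1.96) = 21% |

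The difference detectable with 90% power is (1.96 + 1.28) × SE: 1.18 SD with 30 per cell and 1.41 SD with 21.

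**The case against.** The strongest reply is that this is loose wording in a condensed article. Section 2.1 declares the factorial, the interaction is estimable from the four cells, a redundant genotype column does not corrupt the group × time test, and an analysis plan may set out the terms properly. It is true that neither the design nor the data are at fault. But section 2.28 is not silent: it enumerates factors and levels, and the enumeration is wrong and at odds with section 2.1. An analysis plan that followed it would inherit the fault.

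A second reply is that the Introduction frames the aim as the diet effect in carriers, which the post hoc comparison of satiety with control in the high-risk class partly serves. That stands for that aim. It does not answer the abstract's question whether "tailoring nutritional care based on genetic risk for obesity enhances weight loss", nor support the conclusion in section 4.

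A reader might go further and infer that the diet effect itself is left to an omnibus four-group test, with a loss of power, or that the pairwise comparisons generally confound diet with genotype. The document does not support either reading. On its plain meaning, the one-way ANOVA of changes is already the 1-df diet comparison, and only two of the six pairs mix diet and genotype. A power loss for the diet effect could not be quantified safely in any case, because the 0.50 in section 2.7 is given without its metric.

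**Conclusion.** The model in section 2.28 is wrongly stated. Genotype contributes 0 df beyond the four-level group, and none of the planned terms or contrasts tests whether the diet effect depends on genetic risk, which is what the abstract and section 4 require. This follows from the listed factor levels and needs no numerical assumption. The overall diet effect is covered, and the trial can estimate the interaction, so the error is one of specification.

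The power figures rest on assumed interaction sizes, a single change score with common SD, and equal cells of 30 or 21. They show that the correctly named test would be imprecise: an interaction of half an SD would probably be missed, and a non-significant result would not show that genotype is irrelevant.

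**What to change.** In section 2.28:

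- Replace the four-level group and the separate genotype factor by diet arm (control/satiety) × genotype (LR/HR) × time, matching section 2.1.
- Keep the control-versus-intervention comparison of change as the test of the diet.
- Name the 1-df diet × genotype contrast on weight change at a stated visit, with its confidence interval, as the test of the genetic question.
- Report the diet effects within low and high risk as estimates, not as separate tests from which a difference is inferred.
- Say there and in section 4 that a conclusion on genetic guidance will be drawn only from the interaction.

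The cost is rewording. No df are lost, and no new data or participants are needed. The downside is the limited precision shown above. The plan should acknowledge it, so that a wide interval is not read as evidence of no interaction. The change should be made before outcome data are examined by arm.

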### Sample size calculation

2.7

For a sample calculation, analyses were performed assuming a weight loss of 5%–10% as the primary outcome, a significance level of 5%, a test power of 90% and an effect size of 0.50. Thus, considering a 30% sample loss, the sample size is 30 per group, totalling 120 participants. The G*Power 3.0.10 analysis programme was used, adopting an ‘a priori’ analysis using the variance test (ANOVA) for repeated measures.

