### Randomisation and allocation

2.8

Based on the genotypes, an unweighted risk genetic will be calculated, obtained by summing the number of identified risk alleles. Each genotype will be coded as 0, 1 or 2, according to the absence, presence in heterozygosity or homozygosity of the risk allele, resulting in a total genetic risk scoring (GRS) ranging from 0 to 8. From there, a sum of risk alleles will be made, and it will be pre‐categorised as high (≥3 variant risk alleles) or low (<3 variant risk alleles).^18^

Randomisation will be performed using the MinimPy® software (version 3.0), employing the minimisation method to ensure balance among the four groups in terms of sex, risk genetic (LR and HR), age range (20–39 years; 40–55 years) and BMI range (27.0–29.9 kg/m^2^; 30.0–34.9 kg/m^2^; 35.0–40.0 kg/m^2^).

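### Allocation is minimised on sex, genetic risk, age and BMI, but the stated diet comparison adjusts for none of sex, age, BMI or baseline value, which loses precision if those factors are prognostic

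*Protocol article*

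**What the plan says.** Section 2.8 (Randomisation and allocation) describes software "employing the minimisation method to ensure balance among the four groups in terms of sex, risk genetic (LR and HR), age range" and BMI range. Age has two bands and BMI three.

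Section 2.28 (Statistical analysis) names three kinds of model for the outcomes:

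- "A mixed ANOVA will be applied to determine the effects of groups", where the terms are the four diet-by-risk groups, time (baseline, 12 and 18 weeks) and genotype. Post hoc comparisons use Bonferroni-adjusted marginal means.
- A one-way ANOVA that "will be used to compare changes in the evaluated variables between the control and intervention groups".
- Regressions of an exploratory kind, on which the section says: "Linear and nonlinear regression models will be explored to estimate the association between variables with significant correlation".

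Section 2.7 (Sample size calculation) assumes "a significance level of 5%, a test power of 90% and an effect size of 0.50" and concludes: "considering a 30% sample loss, the sample size is 30 per group, totalling 120 participants".

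**The concern.** Minimisation makes the arms more alike on its factors than chance would. If those factors predict weight change, the difference between arms varies less from trial to trial than it would under simple randomisation. An analysis without the factors does not see this. It leaves their variance in the residual, so the standard error describes a noisier trial than the one that was run. Confidence intervals are then too wide and the test rejects less often than its nominal level.

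The baseline value raises a related question. Subtracting baseline to form a change is not the same as adjusting for baseline. For outcomes with only moderate baseline to follow-up correlation, the change analysis is the less precise of the two.

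What is at stake is precision and power, in a trial that expects to keep 84 of 120 participants.

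**Working it through.** **Inputs from the article.** 120 randomised with 30% loss: 120 × 0.70 = 84, or 42 per diet arm if loss is even. Two-sided 5% is assumed, since sidedness is not stated. The minimisation factors use 1 (sex) + 1 (risk) + 1 (age) + 2 (BMI) = 5 degrees of freedom.

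**Assumed.** R², the share of variance in change explained by the four factors; the prevalence of each factor level; a biased-coin probability of 0.8 in the minimisation. The article gives none of these.

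**The plan's own figure.** The stated 120 was tried first. Four groups, three times, an effect size f of 0.50 and an assumed correlation of 0.5 give 44 in total for the between-group effect, or 64 after allowing for loss, so 120 is not reproduced on those inputs. That is a separate matter. Here 120 and 84 are taken as given.

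**Which model adjusts for what.**

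| Analysis in 2.28 | Genetic risk | Sex, age, BMI | Baseline value |
|---|---|---|---|
| Mixed ANOVA | yes | no | only as a level of time |
| One-way ANOVA of change | no (yes if run on four groups) | no | only by subtraction |
| Regressions | exploratory associations, not a diet comparison | | |

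**Closed form, in SD units.** Unadjusted SE = √(2/n): √(2/42) = 0.218 and √(2/60) = 0.183. Adjusted SE ≈ √(2(1−R²)/n). For R² = 0.10, 0.20, 0.30 this gives 0.207, 0.195, 0.183 with 42 per arm, and 0.173, 0.163, 0.153 with 60 per arm.

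**Simulation.** Minimised allocation on the four factors, 4,000 runs per setting, comparing the unadjusted ANOVA with a model containing the factors.

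| N | R² | True SD of estimate | Unadjusted SE | Ratio | Adjusted SE | Type I, unadjusted | Type I, adjusted |
|---|---|---|---|---|---|---|---|
| 84 | 0 | 0.217 | 0.218 | 1.003 | 0.219 | 4.7% | 4.5% |
| 84 | 0.10 | 0.208 | 0.218 | 1.050 | 0.208 | 4.15% | 4.8% |
| 84 | 0.20 | 0.196 | 0.218 | 1.109 | 0.195 | 2.65% | 4.8% |
| 84 | 0.30 | 0.189 | 0.218 | 1.156 | 0.183 | 2.5% | 5.0% |
| 120 | 0 | 0.181 | 0.182 | 1.007 | 0.182 | 5.0% | 5.1% |
| 120 | 0.10 | 0.176 | 0.182 | 1.036 | 0.173 | 4.05% | 5.6% |
| 120 | 0.20 | 0.165 | 0.182 | 1.105 | 0.163 | 3.0% | 4.9% |
| 120 | 0.30 | 0.157 | 0.183 | 1.160 | 0.153 | 2.1% | 5.0% |

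Monte Carlo error on a 5% rate is √(0.05 × 0.95/4000) = 0.34 percentage points. The adjusted SEs match the closed form.

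**Small R².** At R² = 0.05 the SE ratio is at best √0.95 = 0.975. A pessimistic charge for five degrees of freedom is √(82/77) = 1.032 with 84 analysed, and 0.975 × 1.032 = 1.006, which leaves no gain. With 120 analysed it is 0.975 × √(118/113) = 0.996.

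**Power, for an illustrative difference of 0.5 SD between diet arms.** With 42 per arm: 63.0% unadjusted, then 67.6%, 72.6%, 78.2% for R² = 0.10, 0.20, 0.30. With 60 per arm: 78.2%, then 82.3%, 86.5%, 90.5%. If the article's 0.50 is Cohen's f, the two-arm difference is 1.0 SD. Unadjusted power with 42 per arm is then already 99.6%, and only interval width is at stake.

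**Baseline value.** With equal variances and correlation r, change has variance 2σ²(1−r) and ANCOVA σ²(1−r²), a ratio of (1+r)/2. For assumed r = 0.5, 0.7, 0.9 this is 0.75, 0.85, 0.95. The gain is small for an outcome as stable as weight is likely to be, and larger for noisier markers.

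**The case against.** The strongest reply is that the one-way ANOVA is listed after the mixed ANOVA, and that the sample size rests on repeated-measures ANOVA. In the mixed model genetic risk is present and baseline enters as a level of time. This stands in part: for that model the point narrows to sex, age, BMI and proper baseline adjustment. Baseline as a level of time still makes the group-by-time effect a comparison of unadjusted change. If the one-way ANOVA is meant for all four groups, it too absorbs genetic risk, but nothing else.

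A second reply is that covariate lists often sit in a full protocol or SAP, which is not shown. So the mixed model's silence on covariates is no defect in itself. The one-way ANOVA is different: the article names a test that cannot carry covariates.

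Third, R² is unknown and could be near zero. That is correct, and it limits the claim about size. Minimisation also balances those randomised, not those who complete. Section 2.13 discontinues non-adherent participants, so the 84-completer rows assume that the balance survives loss. Section 2.27 promises intention-to-treat, for which the 120 rows are the closer guide.

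Three stronger readings are tempting but unsupported.

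- A reader might infer that the log rule in 2.28 ("logarithmic transformation will be applied when distributions deviate from normality") cannot be applied because weight changes are mostly negative. The section never says that change scores are logged. Logging the positive measurement and then differencing is well defined.
- A reader might apply the conservatism to all variance explained by baseline weight. Only bands of BMI and age are minimised, and variance that is not balanced does not make the test conservative. If half of a 30% R² were balanced, the actual error rate would be 2(1−Φ(1.96/√0.85)) ≈ 3.4%.
- A reader might infer bias or false positives. Omitting balanced factors causes neither.

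**Conclusion.** The point holds as one of precision. The article balances on four factors and then states a covariate-free comparison of the diet arms; nowhere does it adjust for sex, age, BMI or the baseline value. If the minimised factors explain 10%, 20% or 30% of the variance in change, the unadjusted SE is too large by about 4–5%, 11% or 16%, and a nominal 5% test runs at about 4.1%, 2.7–3.0% or 2.1–2.5%. The adjusted test stays close to 5%. These figures rest on an assumed R², assumed factor prevalences and an assumed biased coin. At an R² near 0 there is no gain, and near 0.05 little. The treatment estimate is unbiased and type I error is not inflated.

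**What to change.** In section 2.28, replace the one-way ANOVA of change with an ANCOVA of the follow-up value (or percentage change) comparing diet arms, or add the covariates to the repeated-measures model. Adjust for the baseline value of the outcome, sex, age, baseline BMI and genetic risk, and fix the list before the data are seen.

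The cost is a change of wording and about five degrees of freedom. In the simulation at R² = 0 that raised the SE only from 0.2175 to 0.2186 with 84 analysed. Every covariate is already recorded for allocation or at the baseline visit.

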Breakfast protein intake	10% of the daily protein intake^14^, ^15^	20% of the daily protein intake^24^, ^25^
Dietary carbohydrate intake	50%–60% of energy^14^, ^15^	45%–50% of energy^14^, ^15^
Dietary fibre intake	≤25 g/day^14^, ^15^	>30–35 g/day^14^, ^15^
Dietary fat intake	25%–30% of energy^14^, ^15^	25%–30% of energy^14^, ^15^
Dietary saturated fat intake	<10% of energy^14^, ^15^	<10% of energy^14^, ^15^
Dietary monounsaturated fat intake	<10% of energy^14^, ^15^	<10%–15% of energy^14^, ^15^
Dietary polyunsaturated fat intake	<8% of energy^14^, ^15^	<10% of energy^14^, ^15^
Intake of standardised granola (sweet or salty version)	Avoid consuming granola, oats, pumpkin, sunflower, flax and sesame seeds	Daily consumption of one sachet (30 g), which can be divided into two portions per day
Cashew nuts	Avoid consuming nuts	15 g/day
Individual consultations	Activities for the treatment of overweight and obesity	Activities for the treatment of overweight and obesity and techniques for the control of hunger and satiety

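### Section 2.28 fits regressions only to variables already significantly correlated in the same data, which overstates weak slopes and screens out most near-symmetric non-monotone relations

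*Protocol article*

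**What the plan says.** The last paragraph of section 2.28 (Statistical analysis) of the protocol article holds the whole rule: "Linear and nonlinear regression models will be explored to estimate the association between variables with significant correlation". The sentence after it sets one threshold for all tests: "The statistical significance criterion will be *p* ≤ 0.05".

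The correlation coefficient is not named. Earlier in the section, "logarithmic transformation will be applied when distributions deviate from normality", which makes Pearson plausible but does not settle it. The form of the regression model is not given either. The Bonferroni adjustment in the section belongs to the ANOVA, where "estimated marginal means will be used for post hoc comparisons".

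Section 2.7 gives the numbers available: "Thus, considering a 30% sample loss, the sample size is 30 per group, totalling 120 participants".

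**The concern.** The rule uses the outcome of a test on the trial data to decide which associations are then estimated on those same data. Ordinary slopes, p-values and confidence intervals assume that the pair was chosen without looking. Here only pairs with a large enough observed correlation are seen, so three things follow:

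- a slope test may merely repeat the screen;
- the reported slopes of weak associations are biased away from zero;
- a screen that responds to linear or monotone trend is a poor gate for nonlinear models, because it can discard a relation that rises and then falls before any curve is fitted.

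At stake is how far the reported associations among diet, satiety, inflammatory, gene-expression, microbiota and weight measures can be trusted. The comparison of the diets does not depend on this step.

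**Working it through.** The article gives no figure for the correlation or regression step, so there is none to reproduce.

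**Inputs**
- Sample size: 120 randomised with 30% loss (section 2.7), so 120 × 0.70 = 84 completers. Both 84 and 120 are used.
- Threshold: p ≤ 0.05 (section 2.28). Sidedness is not stated; two-sided is assumed.
- True correlation r: not given; 0 to 0.5 assumed.
- Coefficient: not named; Pearson assumed, Spearman as a variant.

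**1. Is the slope test a new test?** In a one-predictor linear regression the slope statistic is t = r√((n − 2)/(1 − r²)), which is also the Pearson statistic. In simulation the two p-values agreed to within 5 × 10⁻¹⁶, and 100% of slopes fitted after a Pearson screen were significant, even at true r = 0. Other readings break the identity. At true r = 0:
- after a Spearman screen, 67% (n = 84) and 75% (n = 120) of linear slopes were significant;
- after a Pearson screen, with one added covariate (assumed correlation 0.5 with the predictor), 56% (n = 84) and 51% (n = 120) were.

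**2. How large is the bias?** Setting t at its critical value and solving gives the smallest |r| that can pass: t/√(n − 2 + t²).
- n = 84: t = 1.989, so 1.989/√(82 + 3.957) = 0.215.
- n = 120: t = 1.980, so 1.980/√(118 + 3.922) = 0.179.

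No smaller standardised slope can be reported. Simulation of screen-then-fit (bivariate normal, SD 1, 30,000 runs per setting) gave:

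| True r | n = 84: share passing | mean slope if passed | ratio to truth | 95% CI coverage | n = 120: mean slope if passed | ratio to truth | 95% CI coverage |
|---|---|---|---|---|---|---|---|
| 0.1 | 15% | 0.260 | 2.60 | 81% | 0.225 | 2.25 | 87% |
| 0.2 | 45% | 0.293 | 1.46 | 94% | 0.258 | 1.29 | 96% |
| 0.3 | 80% | 0.336 | 1.12 | 97% | 0.314 | 1.05 | 97% |
| 0.4 | 97% | 0.407 | 1.02 | 97% | 0.400 | 1.00 | 95% |

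At true r = 0 the mean absolute slope among pairs that pass is 0.26 (n = 84) or 0.21 (n = 120). Coverage is then 0%, because a significant slope's 95% interval excludes zero. Without the screen the mean slopes at n = 84 are 0.10, 0.20 and 0.30 for true values 0.1, 0.2 and 0.3.

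**3. Which nonlinear relations survive the screen?** Assumed true R² = 0.25, 4,000 runs:

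| Shape | Passes Pearson, n = 84 | n = 120 |
|---|---|---|
| Symmetric U | 16% | 16% |
| Asymmetric U | 72% | 84% |
| Exponential | 92% | 98% |
| Saturating | 99.7% | 100% |

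A Spearman screen passes 7% of the symmetric U at either size. A quadratic model fitted without any screen detects that U in 98% (n = 84) and 99.8% (n = 120) of runs.

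**The case against.** The strongest reply is that this is one sentence in a condensed article. It says the models are to be explored, states estimation as the aim, and lies outside the mixed ANOVA that tests the intervention. Section 2.6 lists no association analysis among the outcomes. All of that stands and limits the importance of the point. It does not remove the fault, because the gate is a stated rule rather than an omission, and estimation is what selection on significance distorts.

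Four stronger readings are tempting, and the document does not support them.

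- *Every reported slope is significant by construction.* This needs a Pearson screen and an unadjusted one-predictor model on the same observations. The article names neither the coefficient nor the model, and the variants above give 51% to 75% at true r = 0.
- *The nonlinear models never see what they are meant to find.* Monotone curves pass in 92% to 100% of runs and an asymmetric U in 72% to 84%. Monotone curvature is an ordinary reason to fit such a model. The heavy loss is confined to near-symmetric shapes.
- *The rule creates many false associations.* With an assumed 20 variables there are 20 × 19/2 = 190 pairs, and 190 × 0.05 = 9.5 would pass by chance if none were related. That count comes from testing many correlations, not from the regression that follows. Fitting all 190 pairs unadjusted would yield the same number. Neither the number of variables nor testing of all pairs is stated.
- *Differences between the diets will be reported as biological associations.* Table 1 separates the arms on items such as "Dietary fibre intake", so pooled correlations could reflect arm. But Table 1 gives prescribed targets, not intake distributions, and silence on covariates in a condensed article is not an error. Any size for this effect would rest on assumed arm differences.

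**Conclusion.** The concern holds in limited form. Conditioning regression on a significant correlation in the same data overstates weak slopes by a factor of about 2.3 to 2.6 at true r = 0.1 and 1.3 to 1.5 at 0.2. The factor is 1.05 to 1.12 at 0.3, and the effect is negligible from about 0.4. Interval coverage fails clearly only at the weakest correlations (0% at r = 0, 81% to 87% at r = 0.1) and is close to nominal by r = 0.2. About five in six near-symmetric U-shapes with R² = 0.25 never reach the nonlinear model. The simple linear slope test adds no evidence if the screen is Pearson and the model unadjusted.

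These sizes assume a two-sided 0.05 Pearson screen, bivariate normal data for the slopes, and 84 to 120 participants. The point is minor: it affects an exploratory step and leaves the group comparison as it is.

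**What to change.** In section 2.28, delete the condition that limits regression to significantly correlated variables. In its place:

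- name a short list of predictor–outcome pairs, fixed before analysis (for example, change in a satiety marker against change in weight);
- fit every listed pair whatever its correlation p-value, with diet arm and risk group in the model;
- add a quadratic or spline term where curvature is of interest;
- report all slopes with 95% confidence intervals, label them exploratory, and control the false discovery rate over the list.

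The cost is a change of wording and modest extra analysis. The team must agree the list of pairs beforehand, and fewer associations will be called significant.
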